**Fig. 2 Fig2:**
[figure not shown]
Observation, assessment, and follow-up schedule

After randomization, eligible participants will receive their treatment planning investigations and are followed-up following the same schedule for both intervention group and control group (Fig. 2) until recurrence, other malignancy or death is confirmed. Treatment duration is approximately 6–7 weeks for IMRT group. All the participants in both groups will be followed up at 2, 4, 6, 9, 12, 15, 18, 21 and 24 months after randomization, with specialized examination, imaging examination, blood routine examination and biochemistry, Karnofsky performance scale, recording of treatment and adverse events assessment done each time. Quality of life (QOL) scale will be assessed at 2, 6, 12, and 24 months. Forward radiation adverse reactions will be evaluated at each follow-up appointment except at 2 months after randomization. In addition, pathological diagnosis and PET/CT examination will be considered by the investigator if imaging examinations are inadequate to assess the primary outcome. Radioactive adverse events were classified by The National Cancer Institute-Common Terminology Criteria for Adverse Events (NCI-CTCAE) 4.0 standard. Chronic radioactive damages were classified by the criteria of Radiation Therapy Oncology Group/European Organization for Research and Treatment of Cancer (RTOG/EORTC), with common signs and severity recorded.

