### Sample size estimation

Based on medical record of subjects with inoperable salivary gland malignancies in Peking University Cancer Hospital & Institute and in Peking University School and Hospital of Stomatology, local control rate in 1 year was 81 % among subjects with I-125 PBT, and 45 % among subjects with IMRT. Based on a difference of 36 % between groups on the primary outcome, a total of 72 participants are required to provide 90 % power, with the use of two-sided significance level of 0.05. Assuming a 20 % drop-out rate, approximately 90 subjects (or 45 subjects per arm) will be enrolled.

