### Statistical analysis

Analyses will be made using SAS statistical software (version 9.3, SAS Institute, Cary, NC, USA) by researchers at the Peking University Clinical Research Institute. The primary analyses will be done on an intent-to-treat basis and the last observation carry forward (LOCF) is used for missing values. Descriptive statistics will be used to summarize demographic and clinical characteristics of subjects randomised to the intervention and control group. The difference between two groups on demographic and clinical characteristics, response rate and drop-out rate will be compared using t-tests (or Wilcoxon rank sum test) and chi-square test/Fisher’s exact test as appropriate.

Primary outcome (local control rate in 1 year) analyses will be carried out using chi-squared tests. The survival curves (PFS and OS) are estimated by the Kaplan-Meier method, and log-rank test is used to test the null hypothesis that the respective curves are equal between the two groups. A two-sided significance level of 5 % is used. A covariance model will be used to compare the QOL between two groups by adjusting the difference of baseline. The incidence of adverse events between two groups is compared with the chi-square test/Fisher’s exact test.

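### Late radiation reactions are to be compared as crude proportions; if toxicity assessment ends at recurrence, as one of two conflicting follow-up statements says, this is biased against the arm with better local control

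*Protocol article*

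**What the plan says.** All places are in the protocol article.

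- **Statistical analysis.** "The incidence of adverse events between two groups is compared with the chi-square test" or Fisher's exact test. Kaplan-Meier curves and the log-rank test are named only for PFS and OS.
- **Initial screening, assessment and follow-up** (text below Fig. 2). Both arms follow one schedule "until recurrence, other malignancy or death is confirmed". The same paragraph says that all participants "will be followed up at 2, 4, 6, 9, 12, 15, 18, 21 and 24 months after randomization", with "recording of treatment and adverse events assessment done each time".
- **Same section, late toxicity.** "Forward radiation adverse reactions will be evaluated at each follow-up appointment except at 2 months after randomization". Chronic damage is graded by the RTOG/EORTC criteria, separately from the CTCAE grading of other radiation events.
- **Outcomes.** Safety is a named secondary outcome.
- **Sample size estimation.** "local control rate in 1 year was 81 % among subjects with I-125 PBT", against 45% with IMRT.

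**The concern.** A test on the proportion of patients who ever had an event compares risks fairly only if the arms are observed for similar lengths of time. The trial is sized on a large difference in local control. If recurrence ends the visits, the arm with fewer recurrences is watched longer. Late radiation damage accrues over months, so that arm has more opportunity to show it, even at equal risk per unit of time.

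Two things are at stake. The late-toxicity comparison could produce a false signal against PBT for no reason other than better tumour control. And the late-toxicity proportions in both arms would understate the two-year risk. The Discussion relies on safety, alongside efficacy and quality of life, to judge the clinical value of PBT.

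**Working it through.** **Inputs from the protocol.** One-year local control 0.81 (PBT) and 0.45 (IMRT); last visit at 24 months; 72 evaluable patients (36 per arm) and 90 enrolled (45 per arm).

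**Assumptions, not in the protocol.** Constant hazards; exit from toxicity assessment at local progression; a late-toxicity hazard *r* that is identical in both arms, at 0.1, 0.2 or 0.3 per year.

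**1. The plan's own figure.** Two-proportion formula with pooled variance, mean rate 0.63:

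[1.960 × √(2 × 0.63 × 0.37) + 1.282 × √(0.81 × 0.19 + 0.45 × 0.55)]² / 0.36² = (1.338 + 0.812)² / 0.1296 = 35.7, so 36 per arm, 72 in total; 72 / 0.8 = 90. The sample size reproduces and is not affected by this point.

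**2. Hazards of leaving observation.** h = −ln(0.81) = 0.211 per year (PBT); h = −ln(0.45) = 0.799 per year (IMRT). Still observed at 24 months: 0.81² = 66% and 0.45² = 20%.

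**3. Mean observation to 24 months.** (1 − e^(−2h)) / h:
- PBT: (1 − 0.656) / 0.211 = 1.63 years
- IMRT: (1 − 0.2025) / 0.799 = 1.00 year

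**4. Expected crude incidence at r = 0.2.** r/(r + h) × (1 − e^(−2(r + h))):
- PBT: 0.487 × 0.560 = 27.3%
- IMRT: 0.200 × 0.864 = 17.3%
- True two-year risk in each arm: 1 − e^(−0.4) = 33%

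**5. False rejection of a nominal 5% test.** The same formula at the other hazards, then exact summation over all 2×2 tables:

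| r per year | Crude PBT / IMRT | Chi-squared, 45 | Chi-squared, 36 | Fisher, 45 | Fisher, 36 |
|---|---|---|---|---|---|
| 0.1 | 15% / 9% | 14% | 12% | 7% | 5% |
| 0.2 | 27% / 17% | 21% | 17% | 14% | 11% |
| 0.3 | 38% / 24% | 29% | 24% | 21% | 16% |

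At r = 0.2 with chi-squared and 45 per arm, nearly all of the 21.5% goes against PBT (21.4 points).

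**6. Sensitivity.** A second model starts late reactions at month 3, with a true 24-month risk of 30% or 50%. The ratio of crude incidences is 1.70–1.75. Adding an equal hazard of 0.01–0.03 per month for other exits leaves 1.63–1.72. Assuming no local failures after month 12 leaves 1.57–1.59. Acute events confined to the first 3 months hardly move: 48.9% and 45.8% at a true 50%.

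**7. Do the remedies work?** Simulated with equal late-toxicity risk in both arms:
- Exposure-adjusted rates (late-onset model): rejection 4.9–5.3%.
- Log-rank test on time to first late reaction, censored at recurrence: 4–5%.
- Recurrence as a competing event: about 13%, 19% and 24% at r = 0.1, 0.2 and 0.3. Without other censoring, the 24-month cumulative incidence is then the crude proportion of step 4, so the gap remains.

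**The case against.** **The follow-up text can be read the other way.** A reader might infer that the protocol plainly stops toxicity assessment at recurrence. It does not: the same paragraph has every participant seen to month 24 with adverse events assessed at each visit, and OS needs contact after recurrence. If toxicity grading continues in survivors, most of the bias goes. This stands, and it makes the point conditional. But the only stated stopping rule is the one that names recurrence, and OS needs vital status, not toxicity grades. The text does not settle the matter.

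**The size depends on the test and on the numbers evaluable.** A reader might take 21% as the error rate of the planned test. The protocol allows Fisher's test and expects 20% drop-out. For uncommon events, Fisher's test at 36 per arm rejects in about 5%, so the inflation of the nominal level nearly vanishes. The estimates stay skewed. The toxicity hazards come from no passage.

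**All adverse events might seem affected.** They are not. Crude tables are reasonable for acute toxicity.

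**Such detail belongs in the analysis plan.** Windows and grades do, and their absence is no fault here. But the article fixes both the test and the stopping rule, and an analysis plan that follows both inherits the bias.

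**Conclusion.** The point holds in conditional form. The follow-up statements conflict for toxicity assessment. If assessment ends at recurrence, the stated test is wrong for late reactions, and the bias runs against the arm with better local control. With the plan's own control rates and equal assumed late-toxicity hazards of 0.1–0.3 per year, false rejection ranges from about 5% (Fisher, 36 per arm, lowest hazard) to 29% (chi-squared, 45 per arm, highest hazard).

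This rests on constant hazards, on exit at local progression and on assumed toxicity hazards; the direction held in every scenario tried. There is no bias of this kind if local control does not differ between arms, though the trial is sized on the assumption that it does. The primary analysis is untouched. The change should be made, but the trial does not stand or fall on it.

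**What to change.** 1. State in the follow-up section whether toxicity assessment continues after recurrence, so that the stopping rule and the schedule to month 24 agree.
2. Keep the chi-squared/Fisher comparison for acute events in a fixed early window.
3. If assessment ends at recurrence, compare late (RTOG/EORTC) reactions by exposure-adjusted rates, or by time to first late reaction with Kaplan-Meier and log-rank, censored at the end of toxicity assessment. Do not treat recurrence as a competing event, because that reproduces the crude gap.
4. Alternatively, record late reactions to month 24 regardless of recurrence, flag those that follow further anticancer treatment, and treat death as a competing event.

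**Cost.** Option 3 needs slightly more analysis work and the assumption that leaving at recurrence is non-informative for toxicity. The article does not say that onset dates are recorded, but visit dates suffice. Option 4 avoids that assumption for recurrence at the price of some extra data collection. Neither changes the sample size.

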## Discussion

This trail is conducted to prospectively evaluate I-125 PBT for inoperable salivary gland malignancies in terms of the efficacy, safety and the QOL.

Few studies have investigated the effect of I-125 PBT for inoperable salivary gland malignancies and thus, the evidence regarding I-125 PBT for inoperable salivary gland malignancies is sparse. In recent years, we have been exploring the effectiveness and feasibility of I-125 PBT for inoperable salivary gland malignancies. Our previous studies displayed that I-125 PBT may be one of the most promising treatment for inoperable salivary gland malignancies, but the evidence of these results is not sufficient enough due to limited number of observational studies [23, 24]. The proposed study is a randomised controlled single-centre trial conducted among subjects with inoperable salivary gland malignancies. To our knowledge, it is the first trial to investigate the efficacy of I-125 PBT for subjects with inoperable salivary gland malignancies, and will add to the knowledge base in a number of ways. Not only tumor cells, but also normal cells, are simultaneously killed by radiotherapy. Many side effects are often observed during and after radiotherapy, including lower white blood cell count, general weakness and loss of appetite, mucositis, xerostomia, hearing loss, radiation dermatitis, fibrosis, osteoradionecrosis of the mandible, and injury to optic apparatus. These side effects may lower the QOL of these subjects. In addition to effectiveness, we also investigate safety and QOL. These findings will help to systematically evaluate clinical application value of I-125 PBT.

We set a comparison treatment as the control arm, which will help us to assess the efficacy of I-125 PBT. We choose IMRT as the control arm because of its fewer side effects. IMRT is more precise radiotherapy modality which helps to reduce normal tissue damages compared with conventional external radiotherapy. Although there was no evidence that IMRT could significantly improve the LCR, many studies had shown that IMRT could significantly reduce toxic side effects when used in the head and neck cancer region [29]. This IMRT comparison arm can help to protect patient and improve compliance.

On account of the low prevalence, we will recruit patient with relatively inclusive entry criteria, and anticipate recruiting subjects across the spectrum of histologies and from various inoperable circumstances. These features will improve the generalisability of our findings. On the other hand, subjects will constitute a heterogeneous group, and this could weaken the power of our trial. We have taken a number of steps to reduce selection bias. The trial does not include all relevant subjects (e.g., some subjects are excluded, such as with subtotal resection, T1/T2-staged, and metastatic cancer). In addition, subjects are stratified by tumor size (≤4 cm vs. >4 cm) and neck lymph node metastasis (yes vs. no) to balance random allocation.

The treatment allocation cannot be blinded for participants and study staffs due to different procedures and the visibility of implanted I-125 seed in CT image, which is of course a limitation. However, to reduce observer bias in assessment, all assessment data are collected by research assistants who did not participate in the study; in addition, the primary outcome (response to treatment) will be evaluated by independent assessment board. Further, all statistical analysis will be done by a statistician at Peking University Clinical Research Institute who is not affiliated with the trial.

## Conclusion

The proposed study aims to investigate whether subjects with inoperable salivary gland malignancies will benefit from iodine-125 seed permanent brachytherapy. We will also study the side effects of such treatment.
